## Intervention

### The Millon Marker (MM) test kit and report-back

The MM EDC testing panel consists of 13 metabolites, assessing exposure to EDCs that are commonly found in household and personal products. These chemicals are found in over 90% of the US population (at any one time) [5, 15, 21, 22, 62].

Consented participants will be mailed the MM *Detect and Detox* kit. Upon receipt, participants in the intervention group will 1) engage in a Zoom call with a MM coach to complete a comprehensive 24-hour food/product Lifestyle Audit the day before their urine sample collection, 2) collect first void urine sample the next morning, 3) send back samples via FedEx, 4) receive results as well as personalized recommendations for products and lifestyle changes to reduce EDC exposures, 5) follow the recommendations and make changes to reduce exposures, 7) test again after 3 months. Participants in the control group will complete Steps 2-7, and will receive a report-back with more generalized recommendations. Participants will be guided through this journey from our online instructions, online video tutorials, extensive educational materials, and email communication.

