
These EDCs have relatively short half-lives in the body (i.e. 6 hours to 3 days) [41–43]. Therefore, the fact that most of the population is exposed at any one time [5, 6] indicates ubiquitous and constant exposure sources. However, the rapid elimination from the body also allows for reduction of internal exposure with removal or avoidance of the exposure sources from daily life. Thus, interventions aimed at identifying exposures (through internal and external assessments) and removing them (via personalized recommendations based on exposure levels and lifestyle habits), have the potential to greatly reduce transient EDC exposures, as demonstrated in our previous work [44].

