### Intervention design

Upon consenting and randomization, all participants will be sent baseline surveys and test kits (for baseline urinary exposure levels, and, for a subset, clinical biomarkers). The control group (n = 300) will complete post-test surveys and use the second kits approximately 3 months after the baseline assessment, while the intervention group (n = 300) will complete a Lifestyle Audit and engage in the 8-week curriculum described above. The intervention group will submit the kits 2 weeks after completion of the curriculum (i.e. 3 months after the baseline test). See Fig. 1 for the control vs. intervention group study events.

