### Data collection, management, and analysis

The MM *Detect and Detox* kit is an at-home sample collection service that participants will use to collect their own samples. The mailed kit has the following components: kit box, instruction card with activation code, sterile urine collection cup, biohazard bag with absorbent paper, pre-labeled polymailer. We have built a secure online portal for users to make accounts, register their kits, track the status of their samples, and view their testing results and feedback online. For the Lifestyle Audit, participants in the intervention group will schedule a Zoom call with a MM lifestyle coach to document the food, drinks they consumed, as well as all the products (personal care and household products) they used on the day prior to urine collection. MM’s technology team will oversee the security of MM’s software stack and servers, ensure that the platform is HIPAA-compliant, and oversee the software building and maintenance for this project.

Several emails will be sent to the participants to update them on their sample and report statuses and keep them engaged. FedEx Priority Overnight shipping will be used to ensure the sample quality. The turnaround time for the lab analysis and MM report generation is 2-4 weeks. Three months after submitting their baseline urine sample, participants will be sent the second kit and go through the same process again and submit their second samples. Detailed flow of events is illustrated in Fig. 1.

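### Only the intervention arm is described as having a coach-led exposure audit the day before its post-randomisation baseline urine, so the pre-post endpoint is not protected against an arm-specific reaction to the call

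*Protocol article*

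**What the plan says.** **Order of events.** Under Intervention design: "Upon consenting and randomization, all participants will be sent baseline surveys and test kits". The first urine is therefore a post-allocation measurement in both arms.

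**What precedes the sample.** The section on the MM test kit and report-back numbers the steps. Step 1, for the intervention arm, is to "engage in a Zoom call with a MM coach to complete a comprehensive 24-hour food/product Lifestyle Audit the day before their urine sample collection". Step 2 is to "collect first void urine sample the next morning". For the other arm: "Participants in the control group will complete Steps 2-7". Controls therefore give the same urine sample without the call.

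**A less definite account.** Under Data collection, management, and analysis, "participants in the intervention group will schedule a Zoom call with a MM lifestyle coach to document the food, drinks they consumed" and the products "they used on the day prior to urine collection". This fixes the day being recorded but not the day of the call. Intervention design mentions one Lifestyle Audit, alongside the 8-week curriculum.

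**The second kit.** The data collection section says that participants will "go through the same process again and submit their second samples". It later says again that the second kits are processed in the same way. Neither sentence names a second audit.

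**Endpoint and kinetics.** The primary outcomes are the differences between first and second tests in specific gravity-adjusted concentration, per analyte. Need for EDC intervention gives half-lives of 6 hours to 3 days.

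**The concern.** A baseline taken after allocation is harmless if both arms reach it by the same route. Here one arm has first gone through its food and products with a coach. Intervention design says that participants can view their audit results, and that these tools are meant to help them monitor their own behaviour and exposure. The audit is thus part of what is being tested, and one section places it before the measurement that serves as the untreated reference.

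If the call makes some people avoid an obvious source that day, the intervention-arm baseline falls and the pre-post difference shrinks. If the call is repeated and people react before the second sample, that urine may reflect a day of extra care more than the sustained change that the curriculum aims for. Both would act in one arm only, so randomisation does not balance them, and they could not be separated from the treatment effect afterwards. Specific-gravity adjustment and laboratory blinding do not address this.

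**Working it through.** The plan gives no figure to reproduce. The arithmetic shows only whether one day can matter and in which direction.

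**1. Can one day move the sample?** Half-lives of 6 h and 72 h are from Need for EDC intervention. The time between avoidance and the first void is not stated; 10 to 24 h is assumed. Fraction remaining = 0.5^(t / half-life), if every source stops completely, which is the extreme case.

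| Half-life | t = 10 h | t = 24 h |
|---|---|---|
| 6 h | 0.5^(10/6) = 0.32 | 0.5^(24/6) = 0.06 |
| 72 h | 0.5^(10/72) = 0.91 | 0.5^(24/72) = 0.79 |

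Fast-cleared analytes can move materially overnight and slow ones modestly. Partial avoidance would do less.

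**2. Effect on the pre-post contrast.** Let rb and rf be the call-induced proportional drops in intervention-arm baseline and follow-up urine (assumed; the documents give none). The follow-up/baseline ratio, relative to control, is multiplied by (1 − rf)/(1 − rb). With an assumed true reduction of 25% relative to control:

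- Baseline only, 10%: 1 − 0.75/0.90 = 16.7%.
- Baseline only, 20%: 1 − 0.75/0.80 = 6.3%.
- Equal drops, for example 10% at each: 1 − 0.75 × 0.90/0.90 = 25%, with no bias.
- Follow-up only, 10% or 20%, with no lasting effect: 1 − 0.90 = 10%, or 1 − 0.80 = 20%, of apparent benefit.

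**3. Does cancellation depend on the analysis?** Yes. If follow-up is compared with adjustment for baseline (log-scale slope b), equal drops r leave (1 − b) × ln(1 − r). For r = 20% the remaining ratio is 0.80 at b = 0 and 1.00 at b = 1, and lies between them otherwise. The stated outcome is a difference, so cancellation applies to that outcome if the drops are equal.

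**4. Could a small shift affect the test?** Sample size expects 150 per arm after attrition. The standard error of a between-arm difference in SD units is √(2/150) = 0.115. A spurious shift of 0.1, 0.2 or 0.3 SD in the change would be declared significant at two-sided 0.05 in about 14%, 41% or 74% of trials. The documents give no SD of change, so these shifts cannot be matched to the percentages in step 2.

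**5. Does the plan already cover it?** Expected outcomes and limitations accepts a bias towards the null if users begin reducing exposure at the start, and proposes to examine the literacy and readiness surveys. It treats this as common to all users and does not address a difference by arm on the day before sampling.

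**The case against.** The strongest reply is that the call is described as a record of what was consumed and used. Advice comes later: recommendations are step 4, and problem areas are listed in the report with the laboratory results. No section says that the call changes behaviour. A call late in the day leaves little time to avoid anything before a first void, and the data collection section would allow a call after the sample, in which case no reaction to it could reach that sample. All of this stands, and it limits the point to an unprotected comparison.

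A second reply is that repetition is only inferred. If the audit is repeated and the reactions are equal, they cancel in the stated outcome. If it is not repeated, only the bias towards no effect remains, which is conservative for a superiority claim. This also stands. However, nothing makes the two reactions equal: the first call precedes all teaching and the second would follow the 8-week curriculum. A bias towards no effect still costs the trial its ability to show a benefit.

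A third reply is that a second audit belongs to the package under test. That may be argued for the follow-up urine but does not help the baseline.

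A reader might infer that the arms are known not to be comparable, or that baseline is already a treated value. The documents do not support that, because no reaction is shown or sized. A reader might also infer that every second kit should switch to a post-sample audit. For people whose baseline followed a pre-sample call, that would remove the matching and produce the baseline-only case in the working.

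**Conclusion.** The point holds as a gap in the design. As the test-kit section is written, one arm has an extra, behaviour-oriented contact the day before its post-randomisation baseline urine. The same-process wording suggests that this recurs at the second kit. With short half-lives and a pre-post primary outcome, any reaction enters the between-arm contrast directly.

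Neither size nor net direction can be determined from the documents. With an assumed true reduction of 25%, an assumed baseline-only drop of 10% to 20% gives an apparent 17% to 6%. A follow-up-only drop of the same size gives a spurious 10% to 20% where nothing lasting has changed. Equal drops give no bias in the change score but generally some in a baseline-adjusted comparison. All of this rests on the call preceding the sample, which one section states and another leaves open.

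Two further inferences go too far. Loss between randomisation and baseline could differ by arm, since one arm must schedule a call, but the documents give no figure for it. Nor is moving the point of randomisation needed to remove the problem. This should be fixed; confidence is moderate.

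**What to change.** 1. Reconcile the test-kit, Intervention design and data collection sections on when the audit call takes place and whether it is repeated at the second kit. The data collection section also says that diet is captured before sampling; state the instrument and the arms to which this applies.
2. For participants who have not yet given a baseline sample, hold the audit call after the urine has been collected, as recall of the previous day, at both kits. Both arms then reach each sample by the same route.
3. For participants whose baseline followed a pre-sample audit, keep that order at the second kit so that pre and post conditions match. Flag them and report a sensitivity analysis by audit order.
4. Optionally, in future waves, collect the baseline urine before allocation is disclosed.

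The cost is a protocol amendment and a change in call scheduling. The audit would rely on next-day recall, and procedures would differ between waves, since study events began in September 2024. No sample-size figure changes.

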### The endocrine-disrupting chemical (EDC) environmental health literacy (EHL) curriculum

Our 8-week education curriculum and intervention program is modeled after the Diabetes Prevention Program (DPP) [52] and Omada Health (digital DPP) [63] with the goals of building EDC-related behavioral knowledge and skills for sustained behavior change to minimize exposures. This intervention is intended to help users to 1) better understand their MM Test Kit Exposure Report results, 2) learn about various sources of toxic chemical exposures, 3) learn ways to reduce EDC exposures in various environments, 4) learn how to build behavioral skills to implement and maintain lifestyle changes practically, and 5) feel a sense of community, accomplishment, and accountability. The curriculum is self-directed, with participants required to complete at least 6 of the 8 classes within an 8-week period. See Table 1 for the course overview.

### Online coaching and community forum

For the intervention group, MM will host weekly live coaching sessions (scheduled via Calendly and delivered via Zoom) and individual support (scheduled via Calendly for phone or Zoom calls or text messaging without prior scheduling). The live “office hour”-type coaching sessions will be hosted weekly by trained *Detect and Detox* coaches employed by MM. Participants can drop in at times that are convenient for them. A minimum of 3 sessions will be required. During the sessions, coaches will facilitate group discussions about the course curriculum and answer any questions participants may have during their learning process. The coaches have a minimum of a bachelor’s degree and additional training in environmental medicine.  As we scale, we will also develop standardized coach training manuals to train more coaches. Sessions will be spot-checked to maintain the quality of coaching. Additionally, 10% of the coaching sessions will be recorded and examined for quality control. Participants are also able to email, text and schedule individual phone or video calls with coaches. Coaches will also proactively reach out to participants to support their learning and behavior change progress. This highly engaged model will allow us to support participants throughout their detox journey and provide a high-quality intervention experience. The intervention group will also have access to a MM-moderated online forum (e.g. a private Facebook group), where they can ask questions, share experiences, and engage with the study population community [64, 65]. All participants will retain access to the MM team via email after the trial for any additional questions or follow-up guidance as they continue to implement changes to reduce exposures.

### Intervention design

Upon consenting and randomization, all participants will be sent baseline surveys and test kits (for baseline urinary exposure levels, and, for a subset, clinical biomarkers). The control group (n = 300) will complete post-test surveys and use the second kits approximately 3 months after the baseline assessment, while the intervention group (n = 300) will complete a Lifestyle Audit and engage in the 8-week curriculum described above. The intervention group will submit the kits 2 weeks after completion of the curriculum (i.e. 3 months after the baseline test). See Fig. 1 for the control vs. intervention group study events.

**Fig. 1 Fig1:**
[figure not shown]
Timeline of study events for control and intervention groups

Participants will be able to view the results of their Lifestyle Audit online, as well as their test results and reports. These tools will also help participants to self-monitor their behaviors and exposure reduction progress. All participants (control and intervention) will receive a report back of their urinary exposure levels. The control group will receive a list of general recommendations for exposure reduction based on their EDC exposure levels,while the intervention group will receive a more personalized exposure reduction plan based on the information collected in their Lifestyle Audit.

### Surveys, study measurements and secondary outcomes

EDC levels will be measured at baseline and 3 months. Participants' age, level of education, income, BMI, self-assessed health status, smoking status, alcohol intake, exposure to other toxic substances (e.g. dangerous chemicals, radiation), will be collected via questionnaires after recruitment to the study. We will measure participants’ environmental health literacy (EHL), readiness to change (i.e. readiness to reduce exposures, RtC), and well-being (general health, social support, financial well-being, sleep, stress, and physical activity) at baseline, 3 months (post-intervention surveys), and 6 months (exit surveys) after baseline (see Fig. 1). We will also assess usability and participant satisfaction 3 months after baseline (post-intervention). The EHL survey was adapted from the framework of the “general environmental health scale” section of the survey by Lichtveld et al. [66] which was validated in two geographic areas via exploratory and confirmatory factor analysis. Questions include those regarding individuals’ environmental health knowledge (e.g. “Household dust contains harmful chemicals”), attitudes (e.g. “I am concerned about chemicals I am exposed to through products I buy”), and behaviors (e.g. “I take steps to avoid inhaling cleaning products”). We adapted the RtC survey based on the Transtheoretical Model of Health Behavior Change [67] in which we ask about current efforts and interest in limiting exposure to harmful chemicals. EHL and RtC will be assessed to determine their association with EDC levels, as well as the effect of the intervention on EHL and RtC.

We will also measure participants’ well-being via relevant questions from three validated surveys. General health and sleep will be assessed using questions from the Behavioral Risk Factor Surveillance System; [68] stress will be measured via the Perceived Stress Scale (PSS), [69] and physical activity will be assessed using the International Physical Activity Questionnaire [70, 71]. These secondary health outcomes will be measured at baseline, 3-month and 6-months later to assess changes.

### Clinical biomarker testing

In addition to reducing EDC exposure via report-back/intervention programs, we will also assess clinical endpoints which may be improved by the reduction of EDC exposures as well as our lifestyle behavioral intervention program. To do this, we have partnered with SiPhox, a direct-to-consumer health and disease biomarker testing company [72]. SiPhox uses blood spot technologies to cost-effectively test a wide range of biomarkers involved in cardiovascular diseases and inflammation (apolipoprotein AI (Apo-AI), apolipoprotein B (ApoB), high-sensitivity C-reactive protein (hs-CRP), high-density lipoprotein (HDL), low-density lipoprotein (LDL), triglycerides (TG)), metabolic disease and diabetes (hemoglobin A1C (HbA1c), insulin), hormones and fertility (estradiol, testosterone, free testosterone, prostate-specific antigen, follicle-stimulating hormone (FSH), luteinizing hormone (LH), prolactin, sex-hormone binding globulin (SHBG), anti-Mullerian hormone, thyroid-stimulating hormone (TSH)), stress (cortisol, DHEA), and cancer (hs-CRP, prostate-specific antigen). These biomarkers can indicate risk for disease as well as the extent of ongoing disease states. Changes in these biomarkers can indicate improvement in health and reduced risk for disease. For example, high levels of high-sensitivity C-reactive protein (hs-CRP) indicates chronic inflammation and contributes to many diseases, including cancer, heart disease, lung disease, chronic obstructive pulmonary disease, chronic kidney disease, Alzheimer’s disease, diabetes, obesity, and high blood pressure. Thus reducing hs-CRP can reduce the risk for these diseases.^3^ Similarly, changes in hormone levels, such as increased testosterone, can indicate increased fertility and male reproductive health [73, 74].

We will test 150 individuals in each treatment group (i.e. report-back only group (control) vs. the intervention group (treatment)) for a total of N=300. Sample size estimates were based on a systematic review and meta-analysis of low-fat diets and testosterone measurements in men [74]. Effect sizes across six studies ranged from 0.26-0.7 with an average of 0.37. For a two-tailed paired-samples t-test measuring free testosterone, with an alpha of 0.05 and 95% power to detect an effect of 0.37, a sample size of 97 is required. Multiplying by 1.3 to account for attrition, we arrive at 126 per group. With two groups the total comes to 252 participants. Thus, our sample of 150 participants per group should be sufficient to detect an effect of this size.

We hypothesize that, along with the decrease in EDC exposure, individuals will exhibit improved health biomarkers after EDC report-back. Additionally, we posit that individuals receiving the treatment (i.e. online curriculum, coaching, and community forum support), will show both increased EDC reduction and improved health biomarker levels compared to the control (report-back only) group.

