**Methods:**

We will test a self-directed online interactive curriculum with live counseling sessions and individualized support modeled after the highly effective Diabetes Prevention Program (DPP). Recruiting from the Healthy Nevada Project (HNP), one of the largest population health cohorts in the world, we test the effectiveness of our EDC-specific online intervention curriculum via EHL and RtC surveys and determine changes in EDC exposure before and after intervention in a randomized controlled trial. We will also test for common clinical biomarkers via a commercially available at-home test (Siphox). We will recruit and randomize 300 women and 300 men of reproductive age (total *n*=600) from HNP. Our target population is men and women of reproductive age (18–44 years old).

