### Sample size

We will recruit and randomize 600 participants (1:1 male to female). According to previously published research, this has the power to detect estimated effect sizes for 13 endpoints (9 metabolites and 3 survey analyses), [6, 44, 56, 60, 61] from a sample of *n* = 150 participants per arm (i.e., after 50% attrition down from the original *n* = 300 per arm).

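### The 95% power for clinical biomarkers applies to pre-post change within a group; it does not support the claim that 150 per arm is enough for the comparison between arms

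*Protocol article*

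**What the plan says.** All references are to the protocol article.

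- **Clinical biomarker testing, sizing.** The effect size comes from a meta-analysis of low-fat diets and testosterone in men: "Effect sizes across six studies ranged from 0.26-0.7 with an average of 0.37". The calculation is introduced with "For a two-tailed paired-samples t-test measuring free testosterone, with an alpha of 0.05 and 95% power to detect an effect of 0.37", and the result is 97. Then: "Multiplying by 1.3 to account for attrition, we arrive at 126 per group". Two groups make 252, and the section concludes that the planned 150 per group is adequate for an effect of this size.
- **Same section, hypotheses.** There are two. Biomarkers are expected to improve after report-back, which is a within-group statement. In addition, participants given the curriculum, coaching and forum "will show both increased EDC reduction and improved health biomarker levels compared to the control (report-back only) group", which is a between-arm statement. The Discussion repeats the between-arm expectation for clinical biomarkers.
- **Sample size.** The main calculation rests on 150 participants per arm "after 50% attrition down from the original" 300 per arm.
- **Abstract, Methods.** "We will recruit and randomize 300 women and 300 men of reproductive age". The sex mix of the biomarker subset is not stated.
- **Expected outcomes and limitations.** The biomarker assessment is called exploratory.

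**The concern.** A paired sample size answers whether one group changes from its own baseline. Applying it to each of two groups and adding them up does not size a test of whether one group changes more than the other, because the difference between two independent mean changes has twice the variance of one mean change. The document gives no between-arm calculation for the biomarkers, so its only statement of adequacy is likely to be read as covering the randomised comparison.

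Two further features weaken the figure. The 1.3 factor allows for much less loss than the 50% assumed elsewhere for the same trial. And the effect size was observed in men, while the trial recruits men and women equally.

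At stake is how a null arm comparison would be read. The section EDCs and clinical biomarkers says that clinics and insurers require evidence of biomarker change, and that such evidence could help towards FDA approval and insurance coverage. A non-significant arm difference could be taken for a well-powered negative when it is not.

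**Working it through.** **Inputs from the document.** Standardised effect 0.37 (range 0.26 to 0.7); two-sided alpha 0.05; power 95%; attrition factor 1.3; 150 per arm tested (Clinical biomarker testing). Attrition 50% and a 1:1 sex ratio for the whole trial (Sample size).

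**Step 1: reproduce the plan's figure.** For a paired t-test the noncentrality is d√n on n − 1 degrees of freedom. With d = 0.37, 95% power needs n = 96.9, so 97; power at 97 is 95.0%. Then 97 × 1.3 = 126.1 and 126 × 2 = 252. All three figures reproduce, as a within-group test.

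**Step 2: size the arm comparison.** For a two-sample t-test on change scores the noncentrality is d√(n/2) on 2n − 2 degrees of freedom. Here d = 0.37 is taken as the arm difference in mean change divided by the SD of change, the same scale that the paired calculation uses. The normal approximation is n = 2(1.960 + 1.645)²/0.37² ≈ 190 per arm; the noncentral t gives 190.8, so **191 completers per arm** for 95% power.

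**Step 3: power at the sizes that the document implies.**

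| Completers per arm | Where it comes from | d√(n/2) | Arm comparison | Paired test in one group |
|---|---|---|---|---|
| 150 | no loss | 3.20 | 89% | 99% |
| 115 | 150/1.3 | 2.81 | 80% | 98% |
| 97 | the n behind the 95% | 2.58 | 73% | 95% |
| 75 | 50% loss | 2.27 | 61% | 88.5% |

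With 75 completers per arm, 80% power is reached at d = 0.46.

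**Step 4: attrition.** The factor 1.3 corresponds to a loss of 1 − 1/1.3 = 23%. Because 150 rather than 126 are to be tested, the paired test keeps its 97 completers up to a loss of 1 − 97/150 = 35%. Both are below 50%, and at 50% even the paired test misses its stated 95%.

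**Step 5: men only.** The subset's sex mix is not given. *Assuming* 1:1, there are 75 men per arm. For a testosterone comparison in men at d = 0.37:

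| Men completing per arm | Where it comes from | Arm comparison | Paired test |
|---|---|---|---|
| 75 | no loss | 61% | 88.5% |
| 58 | 75/1.3 | 51% | 79% |
| 37.5 | 50% loss | 35% | 60% |

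**Step 6: sensitivity to the effect and its units.** At d = 0.26, arm-comparison power is 61% with 150 per arm and 35% with 75. At d = 0.7 it is about 100% and 99%. If 0.37 is instead in units of the raw SD, the effect on the change scale is 0.37/√(2(1 − r)), where r is the pre-post correlation. The document gives no r. For illustration, 150 per arm gives 77% at r = 0.3 and 98.5% at r = 0.7; 75 per arm gives 48% and 83%.

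**The case against.** The best defence is that nothing was miscalculated. The section states a within-group hypothesis first, and a paired test fits it. Under Data collection, management, and analysis, the one sentence specific to biomarkers speaks of comparing values before and after the intervention, while the between-arm regression is worded for participants who completed both surveys. On that reading, 126 in each of two groups sizes a pre-post test in each arm. This stands: the figures are right for that purpose, and the test is not wrong for every stated aim. It does not rescue the sufficiency claim for the second hypothesis, which is the randomised comparison and has no calculation of its own.

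It is also fair that 89% is not a ceiling. Besides the raw-SD case, a baseline-adjusted analysis would gain power. With 0.37 on the change-score scale and r from 0.3 to 0.8, it gives 98% to 92% at 150 per arm, 93% to 84% at 115, and 80% to 66% at 75. The document does not name such an analysis. In the other direction, the control arm also receives report-back and is expected to improve, so the arm difference may be smaller than a within-group effect of 0.37.

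Three stronger readings are tempting and not supported:

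- A reader might infer that free testosterone is a men-only endpoint. The panel lists it without a sex restriction; only the source of the effect size is male.
- A reader might take 35% as what the design delivers. At d = 0.37 that figure combines a men-only analysis, an assumed 1:1 subset and the attrition figure of another section.
- A reader might see a threat to the trial's main conclusion. The primary outcomes are the changes in urinary analytes, and the biomarkers are exploratory. That lowers the consequence, although it does not make the adequacy statement true for the arm comparison.

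**Conclusion.** The point holds, with moderate severity. The 97 and the 95% are correct for pre-post change within one group, using an effect size from men. The conclusion that 150 per group is adequate does not carry over to the arm difference. On the change-score scale at d = 0.37, the arm comparison has 89% power at best, 80% under the section's own attrition factor and 61% under the trial's 50%, against 191 completers per arm needed for 95%. These figures assume an unadjusted two-sample comparison of change scores and an arm difference as large as the cited effect.

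Separately, the attrition allowances in the two sections contradict each other. At 50% loss the within-group test falls to about 88%. The men-only figures of 61%, 51% and 35% are conditional on a 1:1 subset, which the document does not state.

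**What to change.** In Clinical biomarker testing:

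1. Say that 97 and 95% power refer to pre-post change within a group, and that the effect size was observed in men.
2. State how 0.37 was standardised (SD of change or raw SD) and, if raw SD, which pre-post correlation is assumed.
3. Add a two-sample calculation for the arm difference in change, with a single attrition figure reconciled with Sample size.
4. Report the power or detectable effect that 150 per arm gives. With 50% loss this is 61% at d = 0.37, or 80% at d = 0.46.
5. Give the intended sex mix of the subset, or limit the testosterone figure to men.
6. Remove the statement of sufficiency for the arm comparison, and repeat in this section that the biomarkers are exploratory.

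The cost is wording only, and no extra participants are needed. The stated power becomes less favourable. Sizing on another marker measured in both sexes is not proposed, because the document gives no effect size for one.
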